## Monitoring

This study will implement a robust data monitoring plan to ensure the collected data’s accuracy, integrity, and confidentiality. Trained research personnel will regularly review and verify the data for completeness and consistency. Additionally, electronic data capture systems will facilitate real-time monitoring and error detection. Any discrepancies or anomalies will be promptly addressed and documented. Given the non-interventional nature of this study and the utilisation of non-invasive data collection methods such as the 24-hour dietary recall, the anticipated risks and harms to participants are minimal. However, participants will be informed of any potential discomfort or inconvenience associated with data collection.

Additionally, measures will be in place to address any unexpected adverse events that may arise during the study. To ensure adherence to established protocols and regulatory guidelines, periodic audits will be conducted by an independent third party. These audits will encompass a comprehensive review of study documentation, data collection procedures, and adherence to ethical standards. Any identified discrepancies or deviations will be addressed promptly, and corrective actions will be implemented to maintain the integrity and validity of the study.

### Ethics and dissemination

#### Research ethics approval

Ethical approval has been carefully addressed in this study, as evidenced by the approval from the following ethics boards. Business, Earth & Environment, Social Sciences (AREA FREC) Committee, University of Leeds, Leeds, United Kingdom, approved with the number: 0484 on 28/04/2023. Similarly, the Rivers State University Teaching Hospital Research Ethics Committee in Port Harcourt, Nigeria, approved with the number: RSUTH/REC/2023316 on 30/03/2023. The study prioritises the protection of participants’ rights and well-being by upholding key ethical principles. All participants will undergo the informed consent procedure to ensure that all participants will receive comprehensive information about the study’s purpose, methods, potential risks, and benefits. All data collected, including questionnaires and personal identifiers, will be treated as confidential. Participants will be assigned unique study IDs, and strict security measures will be implemented.

#### Informed consent

Participants who meet the inclusion criteria will be given the Participant Information Sheet (PIS) and an informed consent form to review independently. After 3 days, study personnel will contact the eligible participants by telephone. If they express interest in participating in the study, they will be asked to sign the informed consent and be given a study identification number.

#### Protocol amendments

Any proposed amendments to the protocol that could impact the conduct of the study, participant recruitment, participant information dissemination, or data analysis will undergo a thorough evaluation. These modifications will be submitted as amendments to the University of Leeds Research Ethics Committee for approval. Following their approval, the updated protocol details will also be communicated to *ClinicalTrials*.*gov*. In cases where changes pertain to enrolled participants, they will be promptly informed of the modifications.

#### Confidentiality and access to data

All data collected will be coded to ensure anonymity, and any identifying information will be securely stored separately from the research data. Throughout data collection, a stringent anonymisation process will be implemented. Participants’ identities will be safeguarded by recording only their randomisation numbers and dates of birth within the data collection tools. Anonymised data will be treated in accordance with the University of Leeds’s Research Data Management Policy, ensuring that sharing, publication, and utilisation are conducted while preserving participant privacy. Any personal, identifiable, or sensitive information will be excluded from publications. Data retention will extend for a minimum of 5 years following publication. Access to the data will be restricted to authorised research team members exclusively.

#### Dissemination plans

The results from this study will be disseminated promptly through various channels to ensure wide accessibility and impact. First, a manuscript detailing the research methodology, results, and conclusions in both phase 1 and phase 2 will be prepared for submission for publication in open-access, peer-reviewed scientific journals. Secondly, presentations will be made at relevant national and international scientific conferences, allowing for engagement with experts in the field and the broader research community. In addition, the results will be summarised in accessible and easy-to-use formats for dissemination to healthcare professionals, policymakers, and the public in Nigeria. Infographics, fact sheets, and webinars will be developed to convey key findings and practical implications for hypertension prevention strategies. The entire protocol, the anonymised dataset and any relevant statistical code will be deposited in the Leeds Research Data Repository and available open access.

## Discussion

Unhealthy dietary shifts from whole foods to highly processed ‘fast food’ options have been linked to the escalating hypertension prevalence in Nigeria. Notably, dietary habits are evolving, marked by increased consumption of meals from eateries and fast-food vendors offering high-fat, high-salt, and high-sugar processed foods [1, 5, 6]. Positive outcomes in hypertension and cardiovascular health have been noted through dietary and lifestyle changes [39–42]. Hence, responsive short dietary assessment tools can swiftly guide healthcare professionals in pinpointing concerns and establishing and tracking dietary goals for patients, including patients with hypertension [43, 44]. Several tools exist for dietary management of cardiovascular disease, type 2 diabetes, hypertension, and non-alcoholic fatty liver disease (NAFLD) that have successfully been developed for clinical use [32, 43, 44]. Nevertheless, many of these tools have been designed and validated primarily in the US and Western European nations, limiting their applicability to Nigeria. Our primary aim is to explore the feasibility, validation, and acceptability of a short dietary assessment tool for evaluating dietary intake among individuals with hypertension in Nigeria.

Currently, no short dietary assessment tool responsive to dietary changes has been developed for hypertensive patients and incorporated into clinical care for the prevention and management of patients with hypertension in Nigeria. Given the practicality of FFQs in settings lacking formal dietetic support and their inherent inclusion of portion sizes to minimise measurement error [15], our aim is to validate a developed short FFQ. The developed FFQ will be informed by the findings of [name] et al. [5] and the Nigeria Nutritional Guidelines [10] culminated in a 27-item tool designed for use with hypertensive patients. We aim to investigate the relative validity of our newly developed short FFQ in relation to 24-hour dietary recall from 50 clinical patients focusing on commonly consumed food in Nigeria. This approach to validate the FFQ has been extensively utilised in the literature by previous studies [32, 45–48].

Feedback from clinical patients and healthcare professionals regarding the FFQ’s feasibility is expected to drive its refinement within a user-friendly clinical context. This could potentially bridge the gap between nutritional guidelines and clinical care, equipping healthcare professionals to systematically assess the dietary intake of patients for diagnostic and preventive purposes and enable clinicians to provide region-specific dietary recommendations, fostering improved disease prevention and management, including hypertension [49]. The anticipated findings from the Intraclass Correlation Coefficient (ICC) analysis and correlations between the FFQ and 24-hour dietary recall (24HR) are poised to illuminate the FFQ’s reproducibility and validity in assessing dietary intake. Strong ICC values and correlations above 0.4 would indicate the FFQ’s reliability and accuracy in capturing habitual dietary patterns, which is crucial for providing accurate dietary advice to patients [44, 50, 51]. The scoring system for the FFQ could offer a practical means of categorising habitual dietary habits. Should the scoring system align with established dietary recommendations and scientific evidence, it could be a valuable tool for clinicians to assess dietary quality and offer tailored dietary guidance to patients. The assessment of the acceptability of the FFQ. Positive feedback could indicate that the FFQ is well-received by clinical patients and that its implementation could be feasible in a clinical setting. This information is essential for potentially integrating the FFQ into routine clinical practice.

The limitations of this protocol include the use of a sole patient cohort and the risk of selection bias, which means that the results may not be generalised to other populations or settings beyond the selected clinical outpatient. Furthermore, reliance on self-reported dietary data through FFQs and 24-hour recalls introduces potential recall bias and measurement error, which may impact the accuracy of dietary assessments [52, 53]. Nonetheless, this study protocol presents several notable strengths. Firstly, the study will address a critical gap in the rising challenge of hypertension in Nigeria and the lack of a brief dietary tool that can be incorporated into clinical care by focusing on the feasibility, validity, and acceptability of a dietary assessment tool explicitly tailored to Nigeria. Secondly, the inclusion of both clinical patients and healthcare professionals in the feasibility assessment phase ensures comprehensive feedback from both user groups, enhancing the applicability and relevance of the dietary assessment tool. Thirdly, should the tool prove to be valid, it holds the potential for adaptation and application in other West African countries. This is attributed to the fact that the tool was crafted based on a food list derived from both Nigerian and Ghanaian national nutrition guidelines [7, 19], as well as findings from our comprehensive systematic review and meta-analysis [5].

In summary, although larger scale studies will be required in more diverse populations in Nigeria, this is a major step towards a culturally-informed dietary questionnaire for clinicians, patients, and researchers that will contribute towards dietary assessment and hypertension prevention in Nigeria.

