### Study aims and objectives

#### Study aims

The overall aim is to deliver a clinically tested and validated short dietary assessment tool that will be ready to use by clinicians, patients, and researchers across Nigeria to provide personalised dietary advice to patients with hypertension and empower its citizens to improve their diet and take an active role in hypertension prevention.

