#### 24-hour dietary recall (24HR)

A 24-hour dietary recall (24HR) will be used to capture the habitual consumption of foods among the participants [20] and used as the reference method to validate the FFQ. The 24HR will be used to collect dietary information of the participants in the past 24 hours using the multiple-pass method [21, 22].

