#### Validation and reproducibility of the FFQ

The FFQ will be administered to clinical patients (*n* = 50) twice (i.e., first and third visits) to quantify the intake of food items. Additionally, an inconsecutive three (3) repeated 24HR, including two weekdays and one weekend day, will be used to collect dietary information from the clinical patients for the past 24 hours using the multiple-pass method [21, 22] at the time of visits and intervals between the two FFQs administrations (**Fig 1**). The reproducibility of the FFQ will be assessed by measuring the level of agreement between the two administrations of the FFQ. Furthermore, the validation will be assessed by evaluating the agreement level between the FFQ and the average of the three 24-hour recalls [32, 33]. Healthcare professionals are not involved in the patient FFQ validation stage.

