#### Development of FFQ score

The FFQ score will be developed using the participant’s dietary intake captured by the FFQ (**Fig 1**). The scoring system will be undertaken similar to the methods used by Framingham and INTERHEART. Briefly, using a random sub-sample of the study population (e.g., 1/3) as a test group, the intake of all 27 food items for each participant will be converted into tertiles, where 1^st^, 2^nd^, and 3^rd^ tertiles represent low, moderate, and high intake for the food item. The association between tertile scores for each of the 27 food groups and hypertension will be individually evaluated in 27 multiple variable regression models in the test group, adjusted for common covariates (e.g., sex, age, etc.). The beta-coefficients for the food item (rounded to the nearest integer) in each multiple variable model, that is significant (p<0.05), will be used as a ‘weight’ to quantify the individual food item’s contribution to hypertension risk. These food tertiles and their weights with then be used to calculate FFQ scores in the other 2/3 of the study population (i.e., validation group) for each individual and then regressed against measures of hypertension. Correlation matrices and forward stepwise regression models will be checked and used to minimise the effect of correlated food items. If the FFQ score is valid, a significant association will be observed between the FFQ score and measures of hypertension.

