### Statistical analysis

Statistical analyses will be conducted using R programming language version 4.3.0 [35] with significance level set at p<0.05. Descriptive statistics will be used to analyse categorical and continuous variables. Categorical demographic variables will be analysed using frequency distribution, while continuous demographic variables will be summarised as mean and standard deviation for normally distributed variables and median and interquartile range (IQR) for non-normally distributed variables. As the frequencies of food groups are not normally distributed, differences in frequencies between the two FFQs (FFQ1 vs. FFQ2) and between the two methods (24 HR vs. FFQ2) in phase 1 will be tested using Wilcoxon’s signed-rank test.

Feasibility and acceptability will be assessed through descriptive analyses, including means and 95% confidence intervals (CI), qualitative feedback, and content analysis of indicators related to the process (e.g., proportion interested, started, completed FFQ) and resource (e.g., time to complete and review, rated performance, and practicality).

The West African Food Composition Table will be used to calculate the nutrient content (macronutrients such as energy, carbohydrates or sugar, proteins, fats, and fibre and minerals such as sodium and potassium) of the foods reported in both the FFQ and 24HR. The mean and distribution of nutrient intakes obtained from the FFQ and 24HR will be calculated, and a comparison will be made to assess the differences using the Wilcoxon signed-rank test. Pearson correlations will be used to calculate the correlation coefficients between the FFQ and 24HR for each nutrient to assess the agreement between the FFQs and 24HR and the reproducibility of the FFQs. Additionally, the agreement between the FFQ and the average of three 24-hour dietary recalls will be estimated using Intraclass Correlation Coefficient (ICC), de-attenuation of the correlation coefficients, or quintile cross-classification analysis and the Bland-Altman plots will be used to visualise the agreement between the recalls and FFQ [36–38].

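### FFQ-recall correlations just above 0.4, with an unquantified strong ICC, are read as the accuracy needed for advice to patients, but a correlation at that floor supports ranking of patients, not accuracy for one patient

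*Protocol article*

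**What the plan says.** All references are to the protocol article.

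- **Discussion.** "Strong ICC values and correlations above 0.4 would indicate" the FFQ's reliability and accuracy for habitual dietary patterns, "which is crucial for providing accurate dietary advice to patients". No value is given for a strong ICC.
- **Study aims.** The tool is meant "to provide personalised dietary advice to patients with hypertension", so the intended use is with individual patients.
- **Sample size and sampling technique.** Here r = 0.5 is the value taken as a good indicator of validity, and it gives the minimum of 29 participants.
- **24-hour dietary recall (24HR)** and **Validation and reproducibility of the FFQ.** The recall is "used as the reference method to validate the FFQ", and validation means "evaluating the agreement level between the FFQ and the average of the three 24-hour recalls".
- **Statistical analysis.** "Pearson correlations will be used to calculate the correlation coefficients between the FFQ and 24HR for each nutrient". The ICC, de-attenuation or quintile cross-classification, and Bland-Altman plots follow. De-attenuation and cross-classification are joined by an 'or', and none of these analyses is tied to a conclusion.
- **Development of FFQ score.** For the score, "the intake of all 27 food items for each participant will be converted into tertiles", and the "tertiles represent low, moderate, and high intake for the food item".

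**The concern.** A correlation describes how well the FFQ orders patients relative to the recall. It is unchanged if the FFQ overstates every intake by a constant amount or factor, and a moderate value leaves wide scatter around each patient. The Discussion nevertheless moves from a correlation above 0.4 to accuracy for advice to patients. The analyses that do bear on individuals (cross-classification and limits of agreement) are partly optional, and no stated conclusion depends on them.

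The document also holds two marks for the same comparison, 0.5 when the study is sized and 0.4 when the result is interpreted, without saying how they relate. A result between them would fall short of the planning mark yet meet the correlation part of the Discussion sentence. It could then be passed to clinicians as support for individual advice that the evidence does not give.

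**Working it through.** **1. The plan's own figure.** Inputs (Sample size section): r = 0.5, two-sided alpha 0.05, power 0.80. Fisher z: n = ((1.960 + 0.842) / atanh 0.5)² + 3, with atanh 0.5 = 0.549, gives 29.01. Exact bivariate-normal power is 0.799 at n = 28 and 0.814 at n = 29, so the stated 29 reproduces. It is the number needed to show that a correlation differs from zero, not the number needed to show agreement for individuals.

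**2. Classification at a given correlation.** Inputs: r = 0.4 as the floor of the Discussion's mark; thirds as low, moderate and high (Development of FFQ score); the recall mean as reference (24-hour dietary recall section). Assumption: bivariate normality, cut on both axes at c = ±0.431. The quantities are:

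- high on both methods, given high on the recall: 3 × P(X > c, Y > c)
- low on the FFQ, given high on the recall: 3 × P(X > c, Y < −c)
- same third: the sum of the three diagonal cells

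At r = 0.4 the diagonal cells are 0.167, 0.120 and 0.167, and each opposite corner is 0.059. So:

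- same third: 0.167 + 0.120 + 0.167 = 0.454, or 45%
- high on both, given high on the recall: 3 × 0.1672 = 0.501, so 50% of high consumers are not classed high
- high on the recall but low on the FFQ: 3 × 0.0594 = 0.178, or 18%
- opposite thirds among all patients: 2 × 0.0594 = 0.119, or about 12% (22% by chance)

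A simulation of 4 million draws gave 0.502 and 0.179 for the two conditional figures.

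| r | same third | high consumers not classed high | high consumers classed low |
|---|---|---|---|
| chance | 33% | 67% | 33% |
| 0.4 | 45% | 50% | 18% |
| 0.5 | 49% | 45% | 14% |
| 0.6 | 53% | 40% | 10% |
| 0.8 | 65% | 28% | 3% |

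With fifths, the grouping named for cross-classification, r = 0.4 leaves 61.9% of the top fifth outside the top fifth by FFQ and puts 6.7% in the bottom fifth. In either grouping r² = 0.16, so the residual SD is √0.84 = 92% of the total SD.

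**3. If the recall mean is not the truth.** The documents give no within- to between-person variance ratio, so λ is assumed to lie between 0.5 and 5. With three recalls and independent errors, r with usual intake = 0.4 × √(1 + λ/3).

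- λ = 0.5: r = 0.43; 48% of high consumers not classed high, 17% classed low
- λ = 2: r = 0.52; 44% and 13%
- λ = 5: r = 0.65; 37% and 8%

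If the errors of the two self-report methods are positively correlated, this correction overstates the correlation with usual intake and the position is less favourable.

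**4. Precision with 50 patients.** An observed r of 0.4 has a Fisher-z 95% CI of tanh(0.424 ± 1.96/√47) = 0.14 to 0.61. About 12% in opposite thirds is 6/50, with a Wilson 95% CI of about 6% to 24%. That interval includes the 22% expected by chance.

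**The case against.** - **The ICC is part of the sentence.** Strong ICC values are named beside the correlation, and the Statistical analysis section applies the ICC to the same FFQ-recall comparison. An agreement ICC cannot be expected to exceed the Pearson correlation, so on a joint reading r = 0.4 would hardly come with a strong ICC and the worst case would not pass. This is a fair reading, but with no value for strong, the text cannot exclude r just above 0.4.
- **The sentence is commentary, not a decision rule.** It calls accuracy crucial for advice; it does not say that 0.4 is sufficient. The Outcomes section makes use conditional on the evaluation, and the limitations concede measurement error. This stands and limits the severity, but not the inference from correlation to accuracy.
- **The figures are approximate.** They describe the floor of the range. The planned Pearson correlations are per nutrient, the thirds belong to the score, and the article itself says food-group frequencies are not normal. All of this stands. The figures illustrate what a correlation of that size means; they do not predict this study's result.
- **The remedy is partly planned.** Cross-classification and Bland-Altman plots are listed, though cross-classification stands after an 'or' and neither is linked to a conclusion.

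A reader might infer more than the documents support. First, 0.4 is not the only mark in the article, since 0.5 appears in the sample size section. Second, classification at r = 0.4 is not almost chance: 18% of high consumers are classed low against 33%. Third, the 50% does not apply to truly high consumers, because the reference is a three-day recall mean. Fourth, a between-person correlation does support ranking of individual patients, not only of groups. Finally, the article does not say that advice will be given from the low, moderate and high categories.

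**Conclusion.** The concern holds in limited form. FFQ-recall correlations just above 0.4 support relative ranking of patients against the 24-hour recall. They do not establish accuracy for one patient, which the stated aim of personalised advice needs. At the floor, 45% are in the same third, 50% of high consumers are not classed high and 18% are classed low. With independent recall errors the last two become about 37-48% and 8-17%. These sizes rest on bivariate normality, the plan's thirds and, for the range, assumed variance ratios of 0.5 to 5. The two marks, 0.4 and 0.5, are also left unreconciled. The change should be made, but the point concerns interpretation and does not affect the data to be collected.

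**What to change.** 1. **Discussion:** say that correlations above 0.4 support relative ranking against the 24-hour recall only, and reconcile 0.4 with the 0.5 in the sample size section.
2. **Statistical analysis:** make cross-classification a fixed analysis instead of one side of an 'or'. Report the shares in the same and in opposite categories with 95% CIs, beside the Bland-Altman limits of agreement.
3. **Claim about patients:** base any statement about advice to individual patients on the results in item 2, or drop it.

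The cost is wording and one table from data already planned. The downsides are a possibly less favourable conclusion and wide intervals with 50 patients (6/50 in opposite thirds gives about 6% to 24%), so the results may not settle the individual-level question.
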